## Abstract

**Background:**

Primary hypertension represents a significant global public health issue and is a major risk factor for severe cardiovascular disease complications. Previous research has indicated that acupuncture, as a relatively safe therapeutic approach, effectively reduces blood pressure and alleviates clinical symptoms.

**Objective:**

This study aims to assess the clinical efficacy and safety of the “HuoXueSanFeng” acupuncture technique in patients with essential hypertension.

**Methods:**

This investigation is designed as a multicenter, randomized, single-blind, sham-controlled clinical trial. A total of 228 participants with essential hypertension will be recruited from 5 tertiary hospitals in China. Participants will be randomly allocated to either the acupuncture group or the sham acupuncture group in a 1:1 ratio. Each participant will undergo treatment 3 times per week over a 6-week period, amounting to 18 sessions in total. Follow-up assessments will be conducted at 1, 2, and 4 weeks post treatment. The primary outcome measures include 24-hour ambulatory blood pressure and immediate in-office blood pressure readings. Secondary outcome measures included the Dizziness Handicap Inventory, the Headache Impact Test-6, and the Pittsburgh Sleep Quality Index. In addition, any adverse events will be documented throughout the study to assess safety.

**Results:**

This study was registered with the China Clinical Trial Registration Center on May 23, 2024. Data collection commenced in July 2024 and is anticipated to conclude in June 2025. Currently, the study is in the data collection phase, with 27 participants recruited, and data analysis has yet to be conducted. The findings of this study are expected to be submitted for publication in November 2025.

**Conclusions:**

The outcomes of this study are anticipated to further elucidate the benefits of acupuncture in reducing blood pressure and to provide more robust evidence for the treatment of essential hypertension using the “HuoXueSanFeng” acupuncture method.

**Trial Registration:**

Chinese Clinical Trial Registry ChiCTR2400084696; https://www.chictr.org.cn/showprojEN.html?proj=229194

**International Registered Report Identifier (IRRID):**

DERR1-10.2196/71850

## Introduction

Hypertension is one of the major risk factors for fatal complications of cardiovascular disease [1-4] and represents a significant public health concern worldwide. Annually, hypertension is responsible for approximately 10.4 million deaths [5]. Therefore, the primary goals of hypertension management are to regulate blood pressure and prevent damage to target organs [6-8]. In 2015, the global prevalence of adults with elevated blood pressure reached 1.13 billion [9], with projections indicating an increase to 1.56 billion by 2025 [10], thereby posing a considerable global health and socioeconomic challenge [11]. The pathophysiology of essential hypertension is intricate, and its etiology is not yet fully elucidated [12]. Although antihypertensive medications have traditionally been the cornerstone of hypertension management, many patients experience inadequate blood pressure control [13]. Approximately 50% of patients discontinue antihypertensive medications within the first year [14], and adherence rates are generally low [15]. Approximately 9% of patients with hypertension discontinue their medication due to adverse side effects [16]. Furthermore, a significant proportion of patients with hypertension continue to experience severe symptoms associated with hypertension, such as headache, dizziness, and insomnia [17-19]. Consequently, the search for effective and low-harm alternative or complementary therapies has become a critical goal in the management of hypertension [20].

Acupuncture, a traditional Chinese medicine intervention, has been practiced for over 2000 years. Currently, several studies have confirmed that acupuncture is effective in lowering blood pressure and relieving symptoms of hypertension [21-24] with little or only minor side effects [25], making it a relatively safe treatment option [26]. It can serve as an alternative or complementary therapy to lower blood pressure in patients who prefer not to use medication [25], thereby improving adherence to treatment. Acupuncture offers advantages such as multitarget, multipathway, and holistic regulation in the management of hypertension [27]. Nonetheless, the current scientific basis for the modulation of primary hypertension by acupuncture is insufficient [28,29]. There are limited intervention trials comparing acupuncture with sham acupuncture in the regulation of hypertension [24]. Previous clinical investigations have predominantly concentrated on examining circadian rhythm alterations in blood pressure, 24-hour ambulatory blood pressure [25,30-32], as well as the combined use of acupuncture and antihypertensive medications [32-36]. These studies indicate that acupuncture may effectively reduce blood pressure in patients with hypertension. In addition, numerous animal studies have demonstrated that acupuncture significantly reduces blood pressure levels in spontaneously hypertensive rats [37,38]. The underlying mechanisms are complex [27,38,39], and it is noteworthy that studies on the relevant aspects of the onset time, effect duration, and dominant effect of acupuncture in lowering blood pressure remain unclear. Therefore, there is an urgent need for large-scale, well-designed multicenter randomized controlled clinical trials to further investigate the efficacy of acupuncture in treating essential hypertension [36].

Academician [name], a distinguished member of the Chinese Academy of Engineering, is recognized as a pivotal figure in the development of modern acupuncture in China. He pioneered the “HuoXueSanFeng” acupuncture technique, specifically designed for the treatment of hypertension, which is grounded in the “Qihai” theoretical framework. This method involves meticulously defined parameters regarding the direction, intensity, duration, and frequency of the twisting force applied during acupuncture, thereby establishing a standardized and replicable antihypertensive protocol to ensure both the operability and consistency of the treatment.

This study aims to conduct a multicenter randomized controlled trial to evaluate the efficacy and safety of the “HuoXueSanFeng” acupuncture technique in managing essential hypertension. The primary objective is to assess the onset and duration of the blood pressure–lowering effects of acupuncture.

## Methods

### Study Design

This ongoing study is a multicenter, randomized, participant-analyst, single-blind, sham-needle-controlled clinical trial of acupuncture for essential hypertension, conducted in 5 tertiary care hospitals in China. Enrollment will begin in June 2024 and will continue through November 2025. The study will enroll 228 participants with essential hypertension, all of whom will be required to voluntarily sign an informed consent form after rigorous screening. Eligible participants will be randomized in a 1:1 ratio into two groups: the treatment group will be treated with the “HuoXueSanFeng” acupuncture method, and the control group will be treated with sham acupuncture. In this trial, all participants will receive acupuncture 3 times a week for 6 weeks, totaling 18 times. Follow-up visits will be made at weeks 1, 2, and 4 after the treatment.

### Participant Recruitment

This study will be conducted at 5 tertiary hospitals in China: Dongzhimen Hospital of Beijing University of Traditional Chinese Medicine, the First Affiliated Hospital of Tianjin University of Traditional Chinese Medicine, the Beijing Hospital of Traditional Chinese Medicine of Capital Medical University, the Third Affiliated Hospital of Beijing University of Traditional Chinese Medicine, and the Dongfang Hospital of Beijing University of Traditional Chinese Medicine. Participants who meet the inclusion criteria will be enrolled in this study, and we will use 3 ways to recruit participants with essential hypertension. First, we will recruit on site by pasting recruitment posters in the outpatient departments of the hospitals. Second, we will disseminate information about this study via WeChat Moments and the hospital's WeChat Official Account; at the same time, we will distribute posters and hold academic lectures at regular intervals at the 5 hospitals and nearby communities. It is important to note that participants will be excluded from the study design, implementation, and outcome assessment throughout the study. The inclusion and exclusion criteria are detailed in Textbox 1.

Inclusion and exclusion criteria.
**Inclusion criteria**
18 years old ≤ age ≤75 years old, both male and female individuals.Those who meet the diagnostic criteria for primary hypertension in the International Society for Hypertension’s 2020 Practice Guidelines, with a hypertension classification of grade 1 and a risk stratification of low to moderate risk; and those who receive acupuncture treatment while their original treatment is not changed;Those who had not taken medication in the past, with an office systolic blood pressure of 140-159 mm Hg and/or a diastolic blood pressure of 90-99 mm Hg; and those who had not changed medication for at least 1 month in the past, with an office systolic blood pressure of 120-159 mm Hg and/or a diastolic blood pressure of 80-99 mm Hg. The types of antihypertensive drugs used are calcium channel blocker+angiotensin converting enzyme inhibitor/angiotensin II receptor antagonist, but no more than two types;Correct understanding of the significance of this clinical study, good compliance with the observations and evaluations of the investigators, and voluntary signing of an informed consent form by the participant himself/herself.
**Exclusion criteria**
Secondary hypertension such as aldosteronism, pheochromocytoma, Cushing’s syndrome, and pregnancy hypertension;Patients with other serious cardiovascular, cerebrovascular, renal, retinal, peripheral vascular complications and diabetes mellitus, blood disorders that are not suitable for acupuncture treatment, combined with diagnosed epilepsy, obstructive sleep apnea, hypoventilation syndrome, and so on;People with mental disorders such as severe anxiety and depression;Pregnant and lactating women;Patients who have received acupuncture treatment since the last 1 month or are participating in other clinical trials.

### Randomization and Assignment Hiding

#### Randomization

Randomization will be performed using stratified block randomization. Randomization will be performed by a statistician not involved in trial implementation or statistical analysis, and random sequences will be generated using the Proc plan program in SAS 9.3 software (SAS Institute). Eligible participants will be randomized in a 1:1 ratio into a needling group and a sham needling group. Stratification by center factor will be applied, with block sizes of 4 or 6.

#### Allocation Concealment

The randomization sequence will be kept by a designated person who is not involved in the screening, recruitment, treatment, or evaluation of participants. The randomized grouping scheme is concealed using sequentially numbered, opaque, sealed envelopes, all prepared by staff independent of the study, and after participants sign informed consent and meet inclusion criteria, the envelopes are opened sequentially by the coordinator in the order of enrollment, and the acupuncturist is informed of the grouping in accordance with the allocation scheme inside the envelope.

#### Blinding Setup

The grouping results were kept confidential to the participants, outcome assessors, and data statisticians. Participants received acupuncture treatments in separate compartments of the clinic to avoid interactions and ensure confidentiality. The steps of each acupuncture operation and the method of administration were kept as consistently as possible to minimize bias. Due to the specificity of acupuncture therapy, it was not possible to blind the physician who performed the needling operation. Similarly, outcome assessors and data statisticians were not involved in the experiment throughout, thus controlling for bias that might be introduced to the trial due to knowledge of the allocation scheme. In addition, patients were asked relevant questions at the end of the last acupuncture session to assess the success of the blinding.

#### Acupuncture Group

In the acupuncture group, the original individualized treatment plan will remain unchanged, and the “HuoXueSanFeng” acupuncture method will be used. All therapists have many years of clinical experience in acupuncture.

Disposable sterile acupuncture needles with a diameter of 0.25 mm and a length of 40 mm (Beijing Zhongyan Taihe Medical Equipment Co, Ltd) will be used. Participants will be placed in a supine position, and the local skin will be routinely sterilized. The acupoints chosen here were bilateral Renying (ST9), Baihui (BL7), Hegu (LI4), ZuSanli (ST36), Taichong (LR3), and Quchi (LI11, right side). The specific localization and operation are shown in Figure 1 and Table 1. The frequency of acupuncture was 120-160 times/minutes, and the twisting amplitude was <90°. Foam pads were fixed on each acupoint, and each acupoint will be administered for 1 minute, after which the needle will be left in place for 30 minutes. The treatment was performed 3 times per week. The measurement time was kept consistent every day, between 9 AM and 11 AM.

**Figure 1 figure1:**
[figure not shown]
Location of acupuncture points.

**Table 1 table1:** Location of acupoints for the acupuncture group.

Acupoints	Locations	Needling methods
Baihui acupoint (GV20)	On the head, the middle of the front hairline is straight up 5 cun^a^.	Baihui stabbed 10-20 mm along the governor vessel, and then twirled and laxated for 1 min.
Renying acupoint (ST9)	In the anterior part of the neck, the upper edge of the thyroid cartilage (approximately at the level of the laryngeal prominence), the anterior border of the sternocleidomastoid muscle, and the pulsation of the common carotid artery are aligned horizontally.	The needle was inserted vertically for 25~40 mm, and the twirling method was applied for 1 min (both sides of the neck).
Quchi acupoint (LI11)	On the lateral side of the elbow, at the midpoint of the line between the Chize point (LU5) and the lateral epicondyle of the humerus. Quchi point was only punctured on the left side, while the right side was used to measure the immediate blood pressure.	The needle was vertically inserted for 25~40 mm, and then twirled and laxated for 1 min (one side of the left arm).
Hegu acupoint (LI4)	On the back of the hand, between the first and second metacarpals, about the midpoint of the radial side of the second metacarpal.	The needle was vertically inserted for 20 ~25 mm, and the twisting and laxation method was applied for 1 min (both sides of the back of the hand).
Zusanli acupoint (ST36)	On the outside of the lower leg, 3 cun below the Du Bi acupoint (ST35), and on the line between Du Bi acupoint (ST35) and JieXi acupoint (ST41).	The needle was inserted vertically for 25~40 mm, and the twirling method was applied for 1 min (both sides of the lower limbs).
Taichong acupoint (LR3)	In the dorsum of the foot, between the first and second metatarsals, in the depression in front of the metatarsal base junction, or touching the arterial pulse.	The needle was inserted vertically for 20~25 mm, and the twisting and laxation method was applied for 1 min (both sides of lower limbs).

^a^1 cun (≈20 mm) is defined as the width of the interphalangeal joint of the patient’s thumb.

The total observation period was 11 weeks, with a baseline period of 1 week, a clinical treatment period of 6 weeks, and follow-up visits of 15 minutes each at weeks 1, 2, and 4 after the end of treatment.

#### Sham Acupuncture Group

Participants in the sham needling group will receive the same duration and frequency of treatment as the needling group, while keeping the original treatment unchanged. Participants will be placed in the supine position and nonmeridian and nonacupuncture points will be selected as the needling location. The specific location and operation method can be found in Figure 2 and Table 2, along with routine sterilization. Foam pads will be fixed on each nonmeridian nonacupuncture point and a disposable sterile comfort needle (customized by Beijing Zhongyan Taihe Medical Instrument Co, Ltd) will be used to pierce through the foam pads to the surface of the skin, simulating needling without actually penetrating the skin, simulating needling without actually penetrating the skin. Participants will be informed that they are receiving a treatment comparing the effects of 2 types of acupuncture to increase their compliance with the treatment while avoiding any deceptive behavior.

**Figure 2 figure2:**
[figure not shown]
Location of non-acupoints.

**Table 2 table2:** Location of non-acupoints for sham acupuncture group.

Non-acupoints	Locations
Non-acupoint 1	In the middle of Touwei (ST8) and Yuyao (EX-HN4)
Non-acupoint 2	In the neck, between the anterior and posterior edges of the sternocleidomastoid muscle, 1 cun above the Futu point^a^ (bilateral neck)
Non-acupoint 3	On the radial side, the midpoint between the medial epicondyle of the humerus and the first process of the ulna (unilateral on the left arm)
Non-acupoint 4	3 cun above the dorsal stria of the wrist, the midpoint of the line between Pianli (LI6) and Zhigou (SJ6); both sides of the forearm
Non-acupoint 5	Three inches below Yanglingquan (GB34), between the gallbladder and stomach meridians (bilateral lower limbs)
Non-acupoint 6	On the dorsum of the foot, the middle of the connecting line between Qiuxu (GB40) and JieXi (ST41); both sides of the lower limbs

^a^1 cun (≈20 mm) is defined as the width of the interphalangeal joint of the patient's thumb. All non-acupoints were directly punctured with a 1 cun blunt head needle through the fixed pad to reach the skin surface, and evenly lifted, inserted and twisted 3 times each, but the skin was not punctured.

#### Adjustment of Antihypertensive Drug Therapy

In this study, participants are required to maintain their current treatment, including antihypertensive medication, after participating in the trial. This will be documented in detail. Discontinuation of medication, adjustment of medication, and use of over-the-counter or herbal medications will not be permitted during the treatment period.

### Outcome Measurements

#### Primary Outcome Measurement

In this study, the assessor will be blinded to the specific subgroups. The primary outcome will include 24-hour ambulatory blood pressure and in-office immediate blood pressure. We plan to measure 24-hour ambulatory blood pressure once at baseline, once a week 6 of treatment, and once a week 4 after the end of treatment. In-office blood pressure will be measured when the patient first arrives at the office, 5 minutes after lying down, and at 5, 15, and 30 minutes after completing the acupuncture operation and 10 minutes after finishing the needle.

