#### Sample Size and Statistical Analysis

The sample size of this study was estimated using the 2-sample *t* test in PASS (Power Analysis and Sample Size Software; NCSS LLC) 11 efficacy. According to existing literature [44], the mean improvement in systolic blood pressure within 24 hours for patients with essential hypertension treated with acupuncture was 8.9 mm Hg, while the mean improvement for those treated with sham acupuncture was 5.4 mm Hg, resulting in a clinical effect difference of 3.5 mm Hg. The SD for each group was 9.9 mm Hg. The sample size calculation assumed a 2-tailed significance level (α) of 0.05 and a statistical power (1-β) of 80%, the total sample size required for acupuncture treatment of mild-to-moderate essential hypertension was calculated to be 102 cases. Accounting for a 10% dropout rate, a total of 228 hypertensive participants needed to be recruited, with 114 participants in each group.

Statistical analyses we will leave to a statistician who is unaware of the groups. Data will be analyzed using the SAS 9.3 and SPSS 29.0 (IBM Corp) packages, and a 2-sided *P*<.05 will be considered statistically significant. We will use the intention-to-treat analysis set for outcome analysis and also validate it using per-protocol analysis to determine if the two results are consistent and inconsistency will require further analysis and discussion. For patients who withdrew from the study midway through the study, baseline data and follow-up data that had been collected before withdrawal were included in the intention-to-treat analysis. Missing values will be interpolated by the last observation carried forward method.

Baseline data on participants’ demographic information and general state characteristics such as age, gender, and disease duration will be represented by descriptive statistics for both groups. We will measure in-office immediate blood pressure values at different time points of the needle prick and 24-hour ambulatory blood pressure values at baseline, week 6 of treatment and week 4 after the end of treatment, and comparisons between groups will be assessed using repeated measures ANOVA.

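### Two blood pressure families are both primary, with no fixed variable, time point or success rule; if either one suffices at P<.05, the false-positive rate is about 7-10% or more

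*Protocol article*

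**What the plan says.** The Abstract (Methods) and the Primary Outcome Measurement section agree that there are two primary families. The Abstract says "The primary outcome measures include 24-hour ambulatory blood pressure and immediate in-office blood pressure readings" and the Methods section says "The primary outcome will include 24-hour ambulatory blood pressure and in-office immediate blood pressure".

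Each family has several measurements:

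- **Ambulatory pressure** is taken "once at baseline, once a week 6 of treatment, and once a week 4 after the end of treatment", which gives two post-baseline times.
- **In-office pressure** is taken on arrival, then "5 minutes after lying down, and at 5, 15, and 30 minutes after completing the acupuncture operation and 10 minutes after finishing the needle". That is six readings per session, and a footnote to Table 3 has them taken in weeks 1 to 6.

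Under Sample Size and Statistical Analysis, a two-sided P<.05 "will be considered statistically significant", and both families are to be compared between groups by repeated measures ANOVA. No alpha split, test order or success rule is given. The sample size rests on one quantity: "the mean improvement in systolic blood pressure within 24 hours for patients with essential hypertension treated with acupuncture was 8.9 mm Hg", against 5.4 mm Hg with sham. That section gives no week for this quantity and does not call it the primary variable.

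The Introduction adds: "The primary objective is to assess the onset and duration" of the pressure-lowering effect.

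**The concern.** A reader of the final report must be able to tell which result decides whether the trial succeeded. Here the plan leaves open which family decides, whether systolic or diastolic pressure counts, at what time, and whether one success is enough. Followed as written, a significant result on either family could be presented as the primary finding, and that choice could be made after the data are seen.

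The power calculation does not cover this choice, because it addresses one variable tested once at .05. The stated objective does not settle the matter either, since onset and duration point to several times. An analysis plan may well work out the mechanics of multiplicity. The list of primary outcomes and the threshold, however, are fixed in the protocol article itself, and they are fixed in a way that leaves the error rate undefined.

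**Working it through.** **1. The plan's own figure.** The document states no overall error rate. Its only related figure is the sample size for 24-hour systolic pressure. Inputs from Sample Size and Statistical Analysis: difference 8.9 − 5.4 = 3.5 mm Hg, SD 9.9 mm Hg, two-sided alpha 0.05, power 80%.

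- n per arm = 2 × (1.960 + 0.842)² × 9.9² / 3.5² = 2 × 7.849 × 98.01 / 12.25 ≈ 125.6, so 126 (127 by the t test).
- The article gives 102, labelled a total. Only read as per arm does it lead to the final figure: 102 / 0.90 = 113.3, so 114 per arm and 228 in all.
- Power at two-sided 0.05 is about 71% with 102 per arm and 76% with 114.

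The 102 therefore does not reproduce from its stated inputs. That is a separate matter. What counts here is that the calculation spends the whole 0.05 on one variable and leaves nothing for a second family.

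**2. Error rate by success rule.** The document fixes neither the number of tests k nor their correlation r, so both are assumptions. For independent tests, the chance of at least one false positive is 1 − (1 − 0.05)^k:

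- k = 2: 1 − 0.95² = 0.0975
- k = 4: 1 − 0.95⁴ = 0.1855

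For correlated tests, equicorrelated two-sided z tests at 1.96 were simulated with 400,000 draws.

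| Tests, any one suffices | independent | r = 0.5 | r = 0.8 | r = 0.9 |
|---|---|---|---|---|
| 2 (one per family) | 9.75% | 9.1% | 7.8% | 7.0% |
| 4 (systolic and diastolic in each family) | 18.5% | 15.6% | 11.4% | 9.4% |

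If both families must be significant, the error is at most 5% without any split.

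**3. Cost of the alternatives for 24-hour systolic pressure.**

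- Splitting alpha as 0.025 + 0.025: n per arm = 2 × (2.241 + 0.842)² × 98.01 / 12.25 ≈ 152.1, so 153 (154 by the t test). Power falls to about 61% with 102 per arm and 67% with 114.
- Fixed order with 24-hour systolic pressure first: it keeps the full 0.05, so power stays at the 71% and 76% of step 1.

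**The case against.** A reader might infer that the trial's false-positive rate is simply well above 5%, and that six readings per session over six weeks plus two ambulatory times multiply into a long list of tests. The documents do not support that. The families are joined by a plain conjunction, and if both must succeed the error is at most 5%. The named analysis, repeated measures ANOVA, can give one overall group test per family, so time points do not by themselves add tests. Repeated pressures in the same person may also be strongly correlated, which pulls the rate towards the low end of the table. It is also fair to say that the sample size already points to 24-hour systolic pressure as the implied primary variable, and that within-session summaries and time-point adjustments are often left to an analysis plan.

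All of that stands, and it limits the size of the problem. It does not remove it. The protocol never says that both families must succeed. It does not say which ANOVA term is decisive: the group effect or the group-by-time interaction. An overall group effect alone would not answer a question about onset and duration. The general provision of t tests or Wilcoxon tests for continuous variables does not exclude blood pressure. The implied primary variable is never named as such.

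A further objection concerns the remedy. Making in-office pressure merely secondary would take the immediate effect out of the primary claim, although onset is part of the primary objective. That objection is sound, and the fix below keeps in-office pressure within the controlled testing order.

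**Conclusion.** The point holds in conditional form. Two families are primary, no variable, time or success rule is fixed, and one unsplit threshold serves both while the trial is sized for 24-hour systolic pressure alone. If either family suffices, the type I error is about 7-10% with one test per family, and about 9-19% if systolic and diastolic are each tested in both. These ranges rest on assumed test counts and on correlations from 0.9 down to zero. It would also be wrong to say that the sample size fixes week 6, because it is tied to no week.

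**What to change.** Before unblinding, amend the Primary Outcome Measurement and Sample Size and Statistical Analysis sections to set this order, with each step tested at two-sided 0.05 and only if the previous one succeeds:

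1. **Primary endpoint:** change in 24-hour systolic pressure at one stated time. Week 6, the end of treatment, is the natural choice, but the sponsor must state it.
2. **Next:** 24-hour systolic pressure at week 4 after treatment, which addresses duration.
3. **Next:** one in-office summary defined in advance, for example the mean change from the supine reading taken before needling, which addresses the immediate effect.

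All other pressure contrasts (diastolic, individual readings, individual weeks) would be supportive. State which model term is tested at each step.

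This holds the overall error at 5%, keeps both outcomes in the confirmatory sequence, and takes no power from 24-hour systolic pressure. The cost is wording, plus one small loss: an in-office claim becomes conditional on the 24-hour result. The article reports 27 participants recruited and no data analysed, so the change can still be made credibly.
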